## Results

Preliminary findings are discussed in the following sections.

### Study characteristics

So far, 62 of the 200 envisioned subjects have been included and data from 22 subjects (15 healthy, 7 AF) have been extracted successfully from the data platform for preliminary analysis (Table 1).

**Table 1 tbl1:** Characteristics of preliminary study participants as of May 2022

Characteristic	Ref	HF	AF
Participants, n	25	15	22
Age, y			
18–39	16	1	0
40–54	3	3	2
55–64	5	5	3
65+	1	6	17
Sex			
Male	12	12	15
Female	13	3	7
BMI			
18.5–24.9	14	3	7
25–29.9	6	6	8
30+	5	6	7
Diabetes			
Yes	0	5	4
No	25	10	18
Smoking			
Yes	0	6	5
No	25	9	17
Hypertension			
Yes	2	8	15
No	23	7	7
Device			
Charge 5	23	8	12
Inspire 2	2	7	10

AF = atrial fibrillation group; BMI = body mass index; HF = heart failure group; Ref = reference group.

### Data show large inter-subject variability

Nonoverlapping 1-hour windows are used to segment heart rate and step counter time series data from 6 subjects. To visualize this high-dimensional data, UMAP^11^ is employed to reduce the data to 2 dimensions while maintaining as much structure as possible. The resulting embedding is displayed in Figure 5, where the distribution of the 2-dimensional UMAP samples are illustrated per subject.

**Figure 5 fig5:**
[figure not shown]
Visualization of heart rate windows (upper image) and step windows (lower image) of 6 subjects. Each window has data of 1 hour (720 time points for heart rate, 60 for steps, respectively). Each high-dimensional window is mapped to a 2-dimensional (2D) location using UMAP.^11^ The contour curves illustrate the distribution of the 2D UMAP samples for each subject, with each color representing 1 of the 6 subjects.

When there is little overlap between subjects, finding a shared pattern among them becomes challenging, making it difficult for a model to learn. As a result, the performance of a machine learning model could be impacted as, during testing, a subject can significantly deviate from the subjects on which the model was trained.

### Heart rate peak alignment in acceleration-deceleration curves indicate difference between 7 AF patients and 15 healthy controls

Next, we explored the heart rate recovery curves after activity (acceleration-deceleration curves).^12^ First a peak is detected, whereafter the start (onset) and end (recovery) points associated to that peak are determined by the minimum heart rate value 5 minutes before and 15 minutes after the peak. The curves are preprocessed by aligning the peaks on the time axis. Additionally, for every subject, the amplitude of the curves is rescaled by the average peak value across all curves for that individual. Figure 6 shows the curves for light activity, defined by a maximum of 20 steps in the 5 minutes preceding the peak and fewer than 10 steps in the 15 minutes after the peak. There are 2 noticeable differences in heart rate patterns between persistent AF patients (in red) and healthy participants (in blue). The standard deviation for AF patients is considerably smaller than that of healthy individuals, and their heart rate recovery is slower, as observed at the 6-minute mark. These distinctions could potentially serve as clinical indicators for atrial fibrillation.

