**Results:**

Enrollment commenced on May 1, 2022, and as of the time of this report, 62 subjects have been included in the study. Preliminary analysis of the data reveals significant inter-subject variability. Notably, we identified heart rate recovery curves and time-delayed correlations between heart rate and step count as potential strong indicators for heart disease.

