**Figure 1 fig1:**

Data analysis pipeline for the ME-TIME study. Included participants (image 1) are given a smartwatch (image 2), which is connected to our data acquisition and storage platform (image 3). The resulting data are then preprocessed (image 4) and put into the data-efficient machine learning model (image 5). AF = atrial fibrillation group; HF = heart failure group; Ref = reference group.

Patients will be asked by their treating physician if they may be approached by an investigator to inform them about the study and potential participation. Healthy participants are recruited through local advertising. Anyone that is interested will then receive an information brochure and informed consent form. At least 2 days after the patient’s receipt of the brochure, the research team will call the patient to schedule an appointment. During this visit, the patient submits the signed consent form and will undergo an ECG and blood pressure measurement that will be analyzed by an experienced cardiologist ([name]). Participants can use their own Fitbit and are otherwise provided with a Fitbit Inspire 2 or Fitbit Charge 5 smartwatch. The device type is assigned to a participant at random to prevent device sampling bias. This will also help to investigate the effect of device type on the performance of the final model. A Fitbit account will be created for all participants which will be connected to a custom-built data platform using the Google Cloud Platform. Our platform features a data portal for research staff to easily register or deregister participants by authorizing a connection to their Fitbit data. Data are extracted daily from Fitbits until the observation period ends and can be analyzed either in the cloud or locally.

All participants will be asked to fill out a survey regarding their health. All participants are monitored for a period of 3 months. After written consent from the 200 subjects, heart rate, step counter, and sleep time series data are extracted from the data platform. Clinical metadata such as age, height, weight, blood pressure at baseline, health survey, and medication use are saved in the Castor (Ciwit BV, Amsterdam, The Netherlands) electronic database.

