### Data characteristics and preparation

The data first undergoes a process involving resampling and artifact removal. In our experience with Fitbit smartwatches, the heart rate is nonuniformly sampled, with a prevalent rate of 0.2 Hz. Therefore, the heart rate is resampled to once per 5 seconds. The step counter is sampled once per minute.

Artifacts involving samples with numerous consecutive constant values are removed, if more than 12 consecutive constant values (equivalent to 1 minute of heart rate samples) are detected. This 1-minute threshold was chosen based on visual inspection, which revealed that heart rate patterns typically occur in the order of minutes, often spanning 10–20 minutes. For sequences with fewer than 12 consecutive missing values, linear interpolation is applied. From the cleaned time series, smaller segments, denoted as windows, are extracted and employed as input for a machine learning model. This process involves a sliding window and windows containing time gaps are excluded. Windows have 2 design considerations: the window size, which determines the number of samples within a window and defines its dimensionality, and the stride, which establishes the step size dictating the shift between windows.

Although the cardiovascular condition of each subject is known, it is unknown in which specific windows these conditions manifest themselves. This is owing to the paroxysmal nature of atrial fibrillation and the variable symptoms of heart failure, which can be influenced by factors like medication adjustments, dietary changes, and the disease’s progressive course. In other words, the subject label is known, but the individual window labels are unknown. This is visually represented in Figure 2a, where the subject label is depicted by the blue/red colors and the unknown window labels are indicated by black dotted lines.

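### The light-activity rule behind Figure 6 sets only upper step limits, so peaks with zero recorded steps qualify and the curves need not show recovery after activity

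*Protocol article*

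**What the plan says.** The subsection opens with what the curves are meant to be: "we explored the heart rate recovery curves after activity (acceleration-deceleration curves". It then gives the order of construction: "First a peak is detected, whereafter the start (onset) and end (recovery) points associated to that peak are determined" from the lowest heart rate in the 5 minutes before and the 15 minutes after. Curves are aligned on their peaks and rescaled within each subject.

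Figure 6 shows the light-activity curves, with the category "defined by a maximum of 20 steps in the 5 minutes preceding the peak and fewer than 10 steps in the 15 minutes" that follow. It compares 7 subjects with persistent AF and 15 without heart disease. The text reports a smaller standard deviation in AF and a slower recovery at 6 minutes, and offers both as possible clinical indicators for AF. The Abstract goes further: "we identified heart rate recovery curves and time-delayed correlations between heart rate and step count as potential strong indicators for heart disease".

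Two statements in Methods bear on what could be done about this. Under Data characteristics and preparation, "The step counter is sampled once per minute". Under Study design and data collection, "heart rate, step counter, and sleep time series data are extracted from the data platform".

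**The concern.** The label says that activity came before the peak, but the rule does not require any. A participant who is asleep or sitting still, with no steps in the whole 20 minutes, satisfies it. Selection starts from a detected heart rate peak, and the step counts serve only to exclude curves with too many steps.

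This affects interpretation. If a signal is aligned on its own peaks, the mean curve rises and falls whether or not there was exertion. For a peak at rest, the speed of the fall describes the persistence of the resting signal, including any smoothing by the device. A group difference 6 minutes after the peak could then come from different resting dynamics, or from the groups contributing different proportions of rest peaks. Neither is heart rate recovery in the sense the article gives the term, and that term carries the claim about a candidate indicator.

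**Working it through.** The article gives no figure to reproduce here. The check is logical, with a little arithmetic.

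**1. The rule as stated.** Let S_pre be the steps in the 5 minutes before the peak and S_post the steps in the 15 minutes after it. A curve qualifies if S_pre ≤ 20 and S_post < 10.

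- Put in (0, 0): 0 ≤ 20 and 0 < 10 both hold, so a peak with no recorded steps qualifies.
- Admissible totals are 0 to 20 before the peak and 0 to 9 after it.
- At the upper limits the mean rates are 20/5 = 4 steps per minute before and 9/15 = 0.6 steps per minute after.
- If the 20 were read as a maximum for each one-minute value, the pre-peak total could reach 5 × 20 = 100, but zero would still qualify.

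**2. Search for a floor elsewhere.** I looked for a minimum step count, a minimum heart rate rise, an activity trigger or a sleep exclusion. None is stated in the peak-alignment subsection, the Figure 6 caption, Data characteristics and preparation, the subsection on multiple-instance learning results, or the Discussion. The sleep series is extracted, but no stated condition uses it here.

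**3. How a difference could arise.** Let p be the share of rest peaks in a group, R(6) the mean rescaled level at 6 minutes for rest peaks, and A(6) the same for activity-preceded peaks. The group mean is p·R(6) + (1 − p)·A(6). Suppose R(6) and A(6) are identical in AF and healthy subjects. The groups still differ by (p_AF − p_ref) × (R(6) − A(6)), which is zero only if the shares are equal or the two kinds of peak fall alike. A difference in R(6) between groups would add to this.

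**4. What is missing for a size.** The article reports neither p, R(6) nor A(6). Table 1 makes unequal shares conceivable, if inactivity differs with age (an assumption): 17 of 22 enrolled AF participants are 65 or older, while 16 of 25 reference participants are 18–39. The ages of the 22 subjects actually analysed are not given.

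**5. Illustration only.** If a peak at rest decays exponentially with time constant τ (an assumption), the share of the rise left at 6 minutes is exp(−6/τ): 0.2% for τ = 1 min, 5% for 2 min, 14% for 3 min and 30% for 5 min. This shows that a visible fall needs no exertion and that its speed depends on the signal. It is not an estimate of any difference between AF and healthy subjects.

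**The case against.** The strongest reply is that this is one exploratory figure, under preliminary findings, in 22 subjects and with cautious wording in the subsection itself. The aim is detection, so a resting pattern that separates AF from healthy subjects could still be useful even if it is misnamed. The peak detector is not described in the article and may require a minimum rise. Zero recorded steps also does not prove the absence of exertion: standing up or arm work may leave no steps.

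Most of this stands, and it limits the point. It does not supply a lower step bound or make the label correct. A minimum rise in the detector would still not show that activity caused the rise.

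A reader might also infer more than the article supports:

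- *That the rule collects mainly spontaneous peaks at rest.* The pre-peak step distribution and the detector are not reported. Many hours of sitting need not yield many detected peaks.
- *That Table 2 is affected.* The MILES model uses peak-aligned curves, but the article does not say that these were restricted to light activity. The model also receives the matching step counts.
- *That the main model inherits the rule.* The Discussion favours preselecting windows on patterns such as this curve. It does not adopt the 20- and 10-step limits, and the planned approach contains no such filter.
- *That rest peaks explain the reported direction.* The decay figures need unequal time constants in the two groups, which the article does not give. Irregular ventricular response would, if anything, suggest short persistence and a faster fall in AF, whereas the article reports a slower one.

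**Conclusion.** The point holds as a defect in a stated definition. The light-activity category has two ceilings, no floor and no sleep exclusion, so it does not select what its label says. The slower fall in AF at 6 minutes cannot be attributed to recovery from activity on the evidence shown. It may be partly that, partly resting dynamics and partly a different mix of peaks.

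The certain part rests only on the rule as printed. The effect on Figure 6 is of unknown size and possibly small, because the share of zero-step peaks is not reported. The conclusion covers Figure 6 and the wording drawn from it. It does not extend to Table 2 or the planned model. It is worth correcting now because the study is ongoing (62 of 200 subjects included at the time of the report) and the Abstract presents recovery curves as a potentially strong indicator.

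**What to change.** Using the step and sleep series already extracted:

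- Split the selected peaks into activity-preceded peaks (pre-peak steps above a stated minimum greater than 0, fixed on training subjects only) and zero-step or sleep peaks. If the minimum exceeds one step, show any peaks between zero and the minimum as their own category.
- Report the distribution of pre-peak steps by group.
- Redraw Figure 6 for each category, and use the term recovery after activity only for the activity-preceded curves.
- If the split is not made, relabel the curves as low-step or resting peaks.
- State whether the MILES input was restricted by this rule. Apply the same split to it only if it was.

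The cost is a re-run of a selection filter on data already held. Each category will have fewer curves per subject, so the means will be noisier, which matters with only 7 AF subjects. Because zero steps does not exclude step-free exertion, zero-step peaks should be reported separately and not discarded.

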**Figure 6 fig6:**
[figure not shown]
Acceleration-deceleration curves during light activity. Red and blue represent data from subjects with persistent atrial fibrillation (n=7) and no heart disease (n=15), respectively. The mean and standard deviation are shown per time point (5 second intervals) for both groups.

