### Step counter and heart rate are correlated with a time delay

Next, we examined whether the cross-correlation function between the heart rate window and its corresponding step counter window is indicative of heart disease. To calculate the correlation, we consider varying window sizes and time differences (lags) between heart rate and steps. The computed cross-correlation matrix for the healthy group, along with the AF and HF patient groups, as shown in Figure 7, shows that the heart rate is correlated with the step counter with 1-minute delay.

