## Discussion

By building a suitable infrastructure with Cloud technology, big data acquired in the study is used to develop data-efficient models using methods from multiple instance and self-supervised learning.

We aim to examine the influence of inter-subject variability on predicting cardiovascular disease and will explore potential methods to mitigate these variabilities.^13^^,^^14^ We expect that patterns indicative of cardiovascular disease become apparent within a timeframe of minutes, hours, or more, considering that consumer-grade wearables have a slower sampling rate compared to the gold standard. We have shown 1 example of such a pattern: the acceleration-deceleration curve. Preselecting windows based on such patterns furthermore mitigates searching through substantial amounts of data that may not provide much information about cardiovascular disease. Inspecting the cross-correlation for several combinations of window size and lag show a different profile for healthy and AF group individuals, showing that it is meaningful to analyze step counter and heart rate together. Big data for heart disease detection requires substantial labeling efforts from physicians.

Using self-supervised learning and MIL, a model can be trained with much fewer labels. Our findings demonstrate this by employing MILES to achieve high specificity, which can aid in ruling out heart disease in individuals experiencing symptoms similar to heart disease but without the condition (ie, false-positives).

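### The recovery-curve and heart rate–step features were chosen by eye after looking and never tested, so the Abstract's wording exceeds what the preliminary data support

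*Protocol article*

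**What the plan says.** **Recovery curves.** In the Results section on heart rate peak alignment, the start and end of each curve are "determined by the minimum heart rate value 5 minutes before and 15 minutes after the peak". The Figure 6 caption adds that "The mean and standard deviation are shown per time point (5 second intervals) for both groups", and that the data come from "subjects with persistent atrial fibrillation (n=7) and no heart disease (n=15), respectively". Two differences are described from the plot. The SD is said to be smaller in AF, with no time point or size attached, and "their heart rate recovery is slower, as observed at the 6-minute mark". The section gives no test, interval, effect size or time point chosen beforehand.

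**Heart rate–step correlation.** In the section on the time-delayed correlation, "we consider varying window sizes and time differences (lags) between heart rate and steps". The number of window sizes and lags is not given, nor is the number of subjects per group. The reported result is a one-minute delay between steps and heart rate. Only the Discussion turns this into a contrast, saying that the AF and healthy profiles differ.

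**Source of the data.** Under Study characteristics, "data from 22 subjects (15 healthy, 7 AF) have been extracted successfully from the data platform for preliminary analysis".

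**How the findings are used.** The Abstract says that both features were identified "as potential strong indicators for heart disease". The Results already feed the peak-aligned curves into the preliminary classifier. The Discussion remarks that "Preselecting windows based on such patterns furthermore mitigates searching through substantial amounts of data".

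**The concern.** A feature picked because it stands out in a plot with hundreds of candidate comparisons needs some allowance for that search before it is called an indicator. With 7 and 15 subjects, pointwise differences that look substantial arise easily from sampling variation. None of the usual safeguards is reported: a feature fixed in advance, an error rate over the family, or a second set of subjects.

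Two consequences follow. First, the Abstract tells readers more than the Results show. The Results say only that the distinctions might serve as indicators for AF, whereas the Abstract adds the word strong and widens the target to heart disease. Second, Algorithm validation draws the external test set at random from all subjects, and nothing in the article keeps out the 22 whose data have already been inspected. If features chosen on those subjects enter the model, a test set that contains some of them is not fully independent.

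**Working it through.** The article states no significance level, p-value or effect size for these comparisons, so there is no figure of its own to reproduce. A two-sided 5% level per point is assumed below.

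**1. Size of the family.** The curve covers 5 + 15 = 20 minutes at 5-second points: 20 × 60 / 5 = 240 points (241 with both ends). With a mean and an SD at each, that is 2 × 240 = 480 comparisons. The same arithmetic gives 3600 / 5 = 720 points per hour, which matches the Figure 5 caption.

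**2. Bound under independence.** 1 − 0.95^240 exceeds 0.9999. This is not realistic, because points 5 seconds apart are correlated, so a simulation is needed.

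**3. Simulation with no true group difference.** One Gaussian curve per subject, 7 versus 15 subjects, 240 points, 6,000 runs per setting. Each point has a pooled t test for the mean and an F test for the SD. The documents give no within-curve correlation, so a range was tried: smooth (squared-exponential), rough (exponential) and constant.

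| Correlation | Any mean or SD difference | Slower AF recovery at some post-peak point | AF/healthy SD ratio below 0.7 over more than 90% of the curve |
|---|---|---|---|
| Smooth, 1 min | 0.94 | 0.34 | 0.00 |
| Smooth, 2 min | 0.77 | 0.20 | 0.00 |
| Smooth, 5 min | 0.47 | 0.10 | 0.00 |
| Smooth, 10 min | 0.31 | 0.06 | 0.03 |
| Smooth, 20 min | 0.21 | 0.04 | 0.08 |
| Rough, 1 min | 1.00 | 0.67 | 0.00 |
| Rough, 2 min | 1.00 | 0.49 | 0.00 |
| Rough, 5 min | 0.94 | 0.28 | 0.00 |
| Rough, 10 min | 0.80 | 0.19 | 0.00 |
| Rough, 20 min | 0.63 | 0.13 | 0.01 |
| Constant | 0.10 | 0.02 | 0.19 |

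The floor of 0.10 is what two tests alone give: 1 − 0.95² = 0.0975. For slower AF recovery, the reference value at one pre-chosen point is 0.025, since only one direction counts.

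**4. What a search costs in effect size.** The standard error factor is √(1/7 + 1/15) = 0.458. One pre-chosen point needs an observed standardised difference of at least t(0.975; 20 df) × 0.458 = 2.086 × 0.458 = 0.95. Bonferroni over 480 uses 0.05 / 480 = 0.000104 and needs about 2.21. That is conservative, because neighbouring points are correlated.

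**5. Window-by-lag grid.** The number of cells k is not stated. If the cells were independent, 1 − 0.95^k gives 0.23 for k = 5, 0.40 for 10, 0.72 for 25 and 0.92 for 50. Real cells are correlated, so this is only an illustration.

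**6. Age.** In Table 1, 17/22 = 77% of AF and 1/25 = 4% of reference subjects are 65 or older. Table 1 covers all 62 included subjects, not the 22 analysed.

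**7. Overlap with the external test set.** Twenty percent of 200 is 40 subjects, or about 40/3 = 13.3 per class. A random draw from the planned 50 AF and 100 reference subjects would be expected to include 7 × 13.3/50 + 15 × 13.3/100 = 1.9 + 2.0, or about 4 of the 22 inspected subjects.

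**The case against.** The strongest reply is that this is a pilot description and does not pretend to be more. The article calls its findings preliminary, says that it explored the curves, uses the word potential, and claims no significance. That is fair, and it is why the point concerns strength of wording and what happens next, not a failed error-controlled analysis. It does not rescue the word strong, or the step from AF to heart disease.

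A reader might go further and infer that the differences are probably chance. The documents do not support that:

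- The probability depends on a correlation that they do not give. For smooth curves with a correlation length of 5 minutes or more it is 0.21 to 0.47.
- The reported pattern is narrower than any difference anywhere. Slower AF recovery after the peak has probability 0.04 to 0.34 for smooth curves and 0.13 to 0.67 for rough ones.
- The SD difference is described for the curve in general, so a search over points explains it poorly. The article also does not say whether that SD is taken across subjects or across curves, so the F test may not match the plotted quantity.
- The one-minute delay is a heart rate–step relation, not a group contrast. Applying 7 versus 15 to Figure 7 is an inference from Study characteristics: its caption names healthy and AF only, while the text also mentions HF.

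A reader might also infer that the plan throws away windows according to the 6-minute contrast. It does not say so. The Discussion remark refers to the acceleration-deceleration curve as a type of segment, which the Results define by peak detection and step limits without the group label. The Methods exclude only windows with time gaps.

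Finally, chance is not the only threat, and a label-shuffling test could pass a difference that is really due to age. That stands, and the remedy has to say so.

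**Conclusion.** The point holds in a limited form. Both features were selected after viewing the plots, without a test, interval or pre-chosen point. The recovery-curve contrast comes from about 240 points with two summaries each in 7 versus 15 subjects; the correlation contrast comes from a grid of unstated size. In every setting tried, the probability of at least one nominal difference along the curve exceeds 5%, from 0.10 to 1.00. So chance cannot be excluded, but it is not shown to be the likely explanation. A real difference could also reflect age. The recovery-curve data compare AF with healthy subjects only, and the Discussion's contrast of correlation profiles is likewise AF versus healthy, so a claim about strong indicators of heart disease goes beyond both.

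The figures rest on an assumed 5% level per point, Gaussian curves, one curve per subject and an assumed correlation. The age figures assume that the 62 included subjects resemble the 22 analysed. The expected overlap of about 4 subjects assumes full recruitment as planned and no rule, outside the article, that keeps the inspected subjects out of the test set.

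**What to change.** 1. **Wording.** In the Abstract, Results and Discussion, drop the word strong, limit the claim to AF versus healthy, and call both features exploratory and hypothesis-generating. State the number of subjects per group and the number of window-lag cells behind Figure 7.
2. **Re-analysis.** Reduce Figures 6 and 7 to one value per subject per time point or cell. Run a permutation test that shuffles subject labels and uses the maximum statistic over all points, and likewise over all cells. This handles the correlation without having to assume it. State that it does not remove confounding by age.
3. **Confirmation.** Fix one recovery feature and one window-lag cell now, and confirm them only in subjects outside the 22 already inspected. Any further subjects used for Figure 7 count as inspected too.
4. **External test set.** Draw it from subjects other than those 22. With full recruitment this leaves 200 − 22 = 178 to draw from (43 AF, 85 reference, 50 HF), against about 13 needed per class. The inspected subjects can still be used for training.

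The cost is a short script on data in hand and some rewording, with no extra subjects or measurements. The downsides are that the preliminary claims become less favourable and the pool for the external test set is slightly smaller.
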